### Suspension criteria

Suspension may occur if significant safety concerns arise, requiring immediate investigation and mitigation measures. If the therapeutic effect is deemed inadequate, a simple physical assessment conducted at the fourth weekwould revealinsufficient efficacy of the trial. In cases of substantial deviations or critical errors in the trial plan, suspension may be necessary to rectify issues and ensure the study proceeds in accordance with the established protocols. 

### Randomization

The randomization process was conducted using Microsoft Excel. Prior to random assignment, the research team collected detailed participant information, including their name, date of birth, participant and center code, and date of inclusion. The randomization list was generated in Excel spreadsheet, where each participant was assigned a random whole number between 1 and 3. After sorting the random numbers, a column was numbered sequentially as “1, 2, 3, 1, 2, 3...” to correspond to the three groups: Group 1 (DT group), Group 2 (M + FE group), and Group 3 (control group). The random numbers were placed in an opaque envelope, which was sequentially numbered. This method ensured transparency and simplicity in the randomization process, with the random list securely stored in a password-protected computer accessible only to the designated researcher responsible for participant assignment. Staff and coaches did not have access to this information.

### Blinding

Participants were intentionally kept uninformed about the specific type of treatment they would receive throughout the course of the trial. Participants might not have effectively differentiated between DT and the other intervention, making the blinding feasible, except for participants in the control group, as they did not participate in any exercise interventions. A strict blinding protocol was maintained, encompassing outcome assessors, data managers, and the statistician. These key personnel remained unaware of the treatment assignments and did not share any study-related information among themselves. To uphold the blinding process, only the designated coaches possessed knowledge of the treatment allocations. It was imperative that the coaches, who were privy to this information, underwent training to effectively communicate with participants while maintaining the blinding of treatment assignments. This stringent blinding procedure was diligently upheld until the point at which the data were locked, ensuring that the integrity of the trial was preserved and that the results remained unbiased and reliable.

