## Methods

### Study design

This study represents an RCT with three distinct groups: the Daoyin Therapy group (DT intervention), the Meditation + Fitness Exercise group (M + FE intervention), and Control group. The Institutional Review Board approval was obtained from the Shanghai University of Sport (Project Number: 102772023RT016). We originally planned to recruit a total of 60 eligible individuals suffering from CNP who would then be randomly assigned to one of these three study arms, ensuring a balanced distribution among them. Prior to participating in the study, all participantswere required to provide written informed consent. The data collection and analysis for outcomes assessment will be carried out by independent researchers who are blinded to participant allocation. The primary treatment center for this trialis situated at Shanghai University of Sport. A schematic representation of the study design can be found in Fig. 1.

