### Data collecting and monitoring

Demographic and baseline characteristic data were gathered by outcome assessors at the time of participant recruitment. In order to maintain data accuracy, two independent data administrators performed data entry and conducted thorough proofreading. Once the data integrity was verified, the database was reviewed and confirmed by a qualified expert and two principal research members. Subsequently, the database was locked, with access restricted to the data administrators and the statistician.

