### Statistical analyses

Demographic and baseline information will be compared among the different groups. The Kolmogorov-Smirnov test will be employed to assess the normality of data. For intragroup hypothesis testing, differences across various time points will be evaluated using repeated measures analysis of variance (RM-ANOVA) for normally distributed data, and Friedman’s test will be employed for data not following a normal distribution. In the case of intergroup hypothesis testing, normally distributed data will be analyzed using multivariate analysis of variance (ANOVA), while non-normally distributed data will be analyzed using the Kruskal-Wallis H test. Generalized Estimating Equation (GEE) model will be used to assess how the primary outcome measures, SC-NPAD, change over time across the three intervention groups. Covariates such as demographic factors, and other relevant variables will be included in the model to account for potential confounding effects. The GEE model will also be employed to examine the effects of the intervention on secondary outcome measures, such as SNPA scores for neck and shoulder posture and function, SF-36 scores for quality of life, and levels of neurotransmitters (5-HT, NE/NA, GABA, ACTH, β-EP, and CGRP) obtained from blood tests. Similar to the primary outcome analysis, this analysis will consider the longitudinal nature of the data and adjust for potential confounders. The GEE model will estimate the average change in outcome measures over time within each intervention group and to compare the differences in changes between the intervention groups and the control group. Interaction terms may be included in the model to examine whether the effects of the intervention vary over time or across different groups of participants. Appropriate adjustments for multiple comparisons will be made if necessary. Statistical significance will be taken at 2-sided *P* < 0.05. Statistical analyses will be performed using SAS 9.4 (SAS Institute Inc., Cary, NC).

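### The stated blind on the statistician ends at data lock, so it does not cover the outcome analysis that the Study design section calls blinded

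*Protocol article*

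**What the plan says.** Three sections of the protocol article bear on who is blinded and for how long.

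- **Study design:** "The data collection and analysis for outcomes assessment will be carried out by independent researchers who are blinded to participant allocation". This covers analysis as well as collection and gives no end point.
- **Blinding:** "A strict blinding protocol was maintained, encompassing outcome assessors, data managers, and the statistician". The same section then sets the limit: "This stringent blinding procedure was diligently upheld until the point at which the data were locked". It goes on to present this as what kept the results unbiased.
- **Data collecting and monitoring:** after double entry, proofreading and expert review, "Subsequently, the database was locked, with access restricted to the data administrators and the statistician".

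Two other sections give context. Under Randomization, the allocation list sits on a password-protected computer that only the researcher responsible for assignment can open. Under Statistical analyses, some modelling decisions are left open in the article: "Covariates such as demographic factors, and other relevant variables will be included in the model" and "Interaction terms may be included in the model". Multiplicity adjustment is conditional on need, with no method named.

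**The concern.** A reader of the Study design section would conclude that the analyst did not know the arms while producing the results. A reader of the Blinding section would conclude only that the analyst did not know them before lock. These are different safeguards. The second protects data cleaning and query handling. The first also protects the modelling decisions taken once the outcome data are complete.

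At stake is whether the article may claim a blinded analysis. The claim matters more where decisions remain to be taken on the data, because an analyst who knows which arm is DT could be influenced by the direction of the result, even without intending it.

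**Working it through.** The article states no figure on this point, so the check is a comparison of sections.

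1. **What must be blinded.** Study design names two activities, data collection and analysis, and says both are done blind.
2. **Who is blinded.** The Blinding section lists outcome assessors, data managers and the statistician. The statistician is the listed role that would run the analysis.
3. **When the blind ends.** The Blinding section says at data lock. No other section extends it.
4. **When the analysis happens.** The data-monitoring section gives the order as entry, proofreading, verification, review, then lock, with the statistician among those who can reach the locked database. The article does not say outright that analysis follows lock, but this order leaves no other natural reading.
5. **Putting these together.** The order is verification, lock (end of the stated blind), analysis. The activity in step 1 falls outside the period in step 3.
6. **Whether another section closes the gap.** None says that arms are coded after lock, that the blind runs through the primary analysis, or that model choices are fixed before the key is released. Equally, none says that the key is handed over at lock.

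**Can a size be attached?** A null simulation was used to see whether masking the arms changes the false-positive rate. Its assumptions do not come from the article: three arms of 18, 3,000 trials, visit correlation 0.5, one weakly prognostic and two null covariates. An unmasked analyst picks the model with the smallest DT-versus-control p-value. A masked analyst picks the model with the smallest three-arm omnibus p-value under codes. DT-versus-control rejection at 0.05 was:

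| Models to choose from | Unmasked | Masked |
|---|---|---|
| One fixed model | 4.7% | same model |
| 8 covariate sets | 6.4% | 6.2% |
| 16 models (8 sets, each on change or on week-12 level) | 12.8% | 12.0% |

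The Monte Carlo standard error of a single rate is √(p(1−p)/3000): √(0.064×0.936/3000) ≈ 0.4 percentage points for the 8-set row and √(0.128×0.872/3000) ≈ 0.6 for the 16-model row. A second null simulation of the same comparison gave 7.5% against 7.4% for 8 models, 12.8% against 11.6% for 16, and 5.4% for the fixed model. The rise above 5% comes from choosing among models. Masking removes 0.1 to 1.2 percentage points of it.

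**The case against.** **The sections can be reconciled.** Saying that a blind held until lock does not say that it was broken at lock. The list is held by one designated researcher, the statistician receives the database and not the list, and no section releases the key. This stands as far as it goes. A reader might infer that the analysis was or will be done unblinded, and the article does not support that. It shows only that the stated blind stops short of the analysis.

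**The Study design wording could be narrower.** Analysis for outcomes assessment might mean scoring or assay reading. That is possible, but the sentence does not say so, and most readers would take it as a claim of blinded analysis.

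**Unblinding at lock is common and not an error in itself.** Agreed. The fault is the disagreement with the other section.

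**The open choices may be closed elsewhere.** A separate SAP, not shown here, could fix covariates, interactions and multiplicity before lock. That would remove most of the consequence but would not make the two sections agree. The open choices are therefore context, not a finding.

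**Not every choice listed can be steered.** "The Kolmogorov-Smirnov test will be employed to assess the normality of data" is followed by a stated rule for parametric or rank tests. Knowing the arms gives little room to manoeuvre there.

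**A reader might infer an inflated type I error from the early end of the blind.** The simulations above do not support that. They measure selection among models, which needs no arm names, and the rates are nearly the same with arms masked. The larger rates also depend on switching between change from baseline and week-12 level, whereas the Statistical analyses section describes the GEE comparison in terms of changes.

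**Conclusion.** The inconsistency is real and minor. The Study design section claims a blinded analysis, and the Blinding section describes a blind on the statistician that ends before the analysis begins. The assurance of unbiased results in the Blinding section therefore does not extend to the analysis step.

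This rests on two readings: that analysis in the Study design section has its ordinary meaning, and that the final analysis is run on the locked database. No numerical effect on the trial's error rates is claimed. Whether the key was in fact released at lock is a matter of record for the trial team and cannot be settled from the article.

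**What to change.** Amend the Blinding section to say that, after lock, the statistician receives the database with arms coded A/B/C; that the model choices are fixed and the primary SC-NPAD analysis is completed under those codes; and that only then does the designated researcher described under Randomization release the key. The Study design section can then stand, with the same end point stated there.

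If the key has already been released, correct the Study design section to say that the analysis was not blinded.

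The cost is a sentence or two of text and a coded arm variable in the analysis dataset. No extra staff are needed, because a separate researcher already holds the list. Coding the arms supports the blinding claim but does not control selection among models. That depends on fixing the model in advance.

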### Interventions

Participants in the DT and M + FE groups attended their respective training classes three times a week for 12 weeks. Coaches instructed and corrected movements during these sessions, teaching Daoyin, meditation, and fitness exercises. Instructional videos were provided to participants for home practice, and participants could send self-recorded videos to coaches via online communication platforms for feedback. Each DT or M + FE exercise classlasted 40 min continuously, excluding warm-up and relaxation time. Assessments were conducted at baseline, at the conclusion of the 12-week intervention period, and again at the 16-week.

Within each class of the DT group, participants underwent Daoyin exercise tailored for neck pain following a 3-step protocol. This protocol included a 10-min warm-up exercise session involving joint and basic Daoyin exercise to prevent sports injuries. The subsequent 40-min Daoyin exercise session comprised guided single, combination, and full-body movements. Finally, a 10-min relaxation exercise sessionfollowed to soothe and relax the body.

Within each class of the M + FE group, participants received a combination of meditation and fitness exercises designed to address neck pain, following a similar 3-step protocol. The warm-up sessionlasted for 10 min and involved joint exercises and basic limb movements. This was followed by a 40-min session consisting of 20 min of guided meditation activities and 20 min of single, combined, and comprehensive fitness exercises focused on neck pain. Lastly, participants engaged in a 10-min relaxation exercise session.

The control group did not receive any specific intervention but were instructed to continue their daily routines. However, participants in the control group were required to attend health education workshops every 2 weeks as part of their study participation.

### Primary outcome measurement

#### SC-NPAD

The simplified Chinese Neck Pain and Disability Scale (SC-NPAD) underwent a rigorous translation and validation process conducted by the Department of Orthopedics at Changhai Hospital, affiliated with the Second Military Medical University. The reliability and validity of the SC-NPAD were systematically assessed. The internal consistency, as indicated by Cronbach’s alpha (α), demonstrated high reliability levels. Furthermore, a factor analysis of the scale revealed its multidimensional structure, comprising four distinct factors: “pain” (items 1–3, 5, 7, 20), “disability” (items 4, 6, 8–11, 15), “neck function” (items 16–19), and “affective and cognitive influence” (items 12–14). The scale exhibited excellent repeatability, with Cronbach’s alpha values ranging from 0.770 to 0.977 for each item [5].

### Secondary outcome measurements

#### MRI

A 3.0T Magnetic Resonance Imaging (MRI) system, equipped with a 32-channel standard head coil, was employed in the imaging procedures at the key laboratory of Shanghai University of Sport. During the MRI scans conducted for the experimental task, participants were positioned in a supine posture and provided with specialized earphones designed to stabilize their heads and minimize the impact of instrument-related noise interference.

#### Blood tests

Blood samples of 8–10 ml were collected from each participant on multiple occasions. The levels of 5-Hydroxytryptamine (5-HT), Norepinephrine/Noradrenaline (NE/NA), and γ-aminobutyric acid (GABA) were quantified utilizing high-performance liquid chromatography (HPLC). The assessment of Adreno-Cortico-Tropic-Hormone (ACTH) was conducted through chemiluminescence immunoassay (CLIA), while β-Endorphin (β-EP) levels were determined using enzyme-linked immunosorbent assay (ELISA). Additionally, the evaluation of Calcitonin-Gene-Related Peptide (CGRP) was performed through radioimmunoassay (RIA). 

#### SNPA

The Static Neck Posture Assessment (SNPA) encompasses several key parameters, including the measurement of the forward head angle (FHA) and forward shoulder angle (FSA). Additionally, the assessment covers the range of motion (ROM) of the neck, which includes flexion, extension, left lateral flexion, right lateral flexion, left rotation, and right rotation.

#### VAS

The Visual Analogue Scale (VAS) assessment procedure entails drawing a 10 cm horizontal line on a sheet of paper. One end of this line is marked as 0, signifying the absence of pain, while the opposite end is marked as 10, representing severe pain. During the assessment, the participant was positioned facing the non-scaled side of the line, ensuring they aligned with the straight line. The participant was then instructed to mark a specific point on the line to indicate both the intensity of pain and the extent of their psychological sensation related to the pain. The healthcare provider, in turn, faced the scaled side of the line and measured the distance from the starting point to the participant’s marked position, which quantified the level of pain experienced. Clinical evaluation categorizes the VAS scores into three ranges: scores from 1 to 3 indicate “mild pain”, scores from 4 to 6 denote “moderate pain”, and scores ranging from 7 to 10 represent “severe pain” [27].

#### SF-36

In 1991, the Chinese version of the Short Form 36 questionnaire (SF-36) was translated by the Social Medicine Teaching and Research Office of the University School of Medicine. Subsequently, Chinese scholars conducted a comprehensive reliability and validity assessment of the Chinese SF-36 version, employing Cronbach’s alpha coefficient as a key metric to evaluate the scale’s internal consistency reliability. The quality of life scale analyzes eight dimensions: Physical Functioning (PF), Role-Physical (RP), Bodily Pain (BP), General Health (GH), Vitality (VT), Social Functioning (SF), Role-Emotional (RE) and Mental Health (MH). In addition to the SF and VT dimensions, the consistency reliability coefficients were computed for the remaining six dimensions, resulting in values ranging from 0.72 to 0.88, signifying good test-retest reliability (ranging from *r* = 0.70 to 0.94). Notably, the validity success rates for all dimensions, except SF, ranged from 75% to 100%, underscoring robust construct validity. Additionally, the discriminant validity success rates also demonstrated strong performance, ranging from 87.5% to 100%. These findings affirm the reliability and validity of the Chinese SF-36 version and support its utility as a comprehensive assessment tool for various dimensions of health-related quality of life [28].

### Safety evaluation

Participant safety was vigilantly monitored throughout each intervention. A team comprising one coach and two responsible assistants collaborated closely with clinicians during every class to provide guidance and ensure safety. In the context of this trial, adverse events are defined as occurrences that meet any of the following criteria: (1) result in severe pain; (2) induce dizziness, severe dizziness, or even syncope; (3) necessitate hospitalization; (4) impede the individual’s ability to work; (5) pose a threat to life. In the event of any adverse events, regardless of their association with the interventions, immediate cessation of treatment would be implemented. Participant experiencing adverse events would promptly receive appropriate remedial treatment. Furthermore, these adverse events would be reported to the relevant responsible entities and ethical committees for evaluation, with a decision made on whether the participant should discontinue participation in the trial. Participant encountering an adverse event would be subject to follow-up until the event has been resolved or until the participant’s condition achieves a state of chronic stability.

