### Follow-up

To assess the short-term efficacy and safety of the intervention, participants underwent a 4-week follow-up period immediately after completing treatments. During this period, participantsdid not receive any additional treatment, and there was no direct researcher supervision. At the end of the 16-week period, participants were required to complete a third test. Furthermore, participants had the opportunity to communicate their clinical symptoms and report any adverse events through in-person discussions, text messages, or via online communication platforms at the designated time points.

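### The adverse event definition leaves out milder, non-disabling harms, and the only active surveillance described is in classes that the control arm does not attend

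*Protocol article*

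**What the plan says.** The Protocol article, Safety evaluation, sets a trial-specific definition with one tier: "adverse events are defined as occurrences that meet any of the following criteria: (1) result in severe pain", and then "2) induce dizziness, severe dizziness, or even syncope; (3) necessitate hospitalization; (4) impede the individual’s ability to work; (5) pose a threat to life". Meeting any one of the five is enough.

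The same section describes how participants are watched: "A team comprising one coach and two responsible assistants collaborated closely with clinicians during every class to provide guidance and ensure safety".

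Under Interventions, "Participants in the DT and M + FE groups attended their respective training classes three times a week for 12 weeks", while "participants in the control group were required to attend health education workshops every 2 weeks".

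Follow-up gives the purpose of the four weeks after treatment: "To assess the short-term efficacy and safety of the intervention". It adds that participants could report symptoms and adverse events in person, by text or online at set time points, and does not limit this to any arm. It also says that researchers did not directly supervise participants in that period.

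Dropout criteria mentions adverse reactions as a reason for withdrawal and, separately, serious adverse events as a reason for removal.

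**The concern.** Apart from dizziness, which counts at any degree, each criterion is a threshold of severity, seriousness or disability. The harms one would expect most often from a neck exercise programme are short-lived soreness, strain and moderate pain flares. These mostly fall below the thresholds. A count built on this definition describes the upper end of the harms and would be read as all of them.

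The other difficulty is how events come to light. Staff with a safety role are described only in classes, and the control arm has none. If a low adverse event count, or a difference from control, is later offered as evidence on safety, part of it will reflect the definition and part the way events were found. The primary efficacy result is not affected.

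**Working it through.** The document states no adverse event rate and no safety sample size, so there is no figure of its own to reproduce. The check has three steps.

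**1. What the definition counts.** The VAS section gives the trial's own pain bands: mild 1 to 3, moderate 4 to 6, and "scores ranging from 7 to 10 represent “severe pain". Safety evaluation does not refer to the VAS, so using these bands is an assumption. On them:
- A participant who goes from 2 to 6 after a class, without dizziness and still working normally, has no adverse event.
- The same participant counts if the flare impedes work, because criterion 4 has no severity floor.
- Muscle soreness or strain counts only if it is severely painful or meets another criterion.

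Set against Dropout criteria, the one-tier definition does not fit the separate use of adverse reactions and serious adverse events. A participant could withdraw for an adverse reaction that Safety evaluation would not count as an adverse event.

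**2. Scheduled contacts over 12 weeks (Interventions).**
- DT: 3 × 12 = 36 classes.
- M+FE: 3 × 12 = 36 classes.
- Control: 12 / 2 = 6 workshops.
- Each exercise arm to control: 36 / 6 = 6. DT to M+FE: 36 / 36 = 1.
- Adding the assessments at weeks 12 and 16, which all arms share: 38 / 8 = 4.75.

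These are ratios of contacts, not of detected events.

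**3. Illustration.** Every rate here is assumed; only the arm size of 20 comes from the document (Sample size).

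*Undercount.* Suppose 30% of 20 participants have any untoward event, so 20 × 0.30 = 6 are expected. Let s be the share that meets the five criteria. Expected recorded = 6s, and the chance of recording none = (1 − 0.30s)^20.

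| s | Recorded of 6 | Chance of none recorded |
|---|---|---|
| 0.10 | 0.6 | 0.97^20 = 54% |
| 0.25 | 1.5 | 0.925^20 = 21% |
| 0.50 | 3.0 | 0.85^20 = 4% |

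*Unequal detection.* With equal true risk and 90% detection in an exercise arm, the recorded ratio of exercise to control is 0.90 divided by the detection rate in control:
- 30% detection: 0.90 / 0.30 = 3.0
- 50% detection: 0.90 / 0.50 = 1.8
- 80% detection: 0.90 / 0.80 = 1.13

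The spread shows that the result is driven by rates the document does not give.

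**The case against.** **Sustained worsening is measured elsewhere.** SC-NPAD and VAS are taken in all arms at weeks 12 and 16, and outcome assessors are described as blinded. This stands for lasting deterioration. It does not cover a flare that comes and goes between assessments.

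**Events can be reported outside classes.** Follow-up offers a route that takes symptoms as well as adverse events and is not limited by arm. This stands and reduces the imbalance. The text does not say whether these reports are prompted, and the narrow definition still decides which of them count as adverse events.

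**A journal article condenses the full protocol.** Event forms and questions put to control participants may be set out there, and the article does not say that controls go unasked. Nor does Statistical analyses describe a comparison of adverse events between arms. That is a fair limit on the surveillance half of the point. It does not reach the definition, which the article states in full.

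**Stronger readings.** A reader might infer three things that the document does not support:
- That harms cannot be compared between any of the arms. DT and M+FE have the same class schedule and the same described monitoring, so only contrasts with control are in question.
- That exercise would appear to have up to six times the events of control. This needs detection in proportion to contacts. Hospital admission, impeded work and threat to life are conspicuous or lasting and can be reported at a later contact, so proportionality is least plausible for the events that now count.
- That every mild or moderate event other than dizziness is excluded. One that impedes work is included.

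**Conclusion.** The point holds in two parts.

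The definition, as written, leaves out mild and moderate flares, soreness and strain that neither cause dizziness nor impede work. Adverse events will be undercounted to that extent in all three arms. This follows from the text alone.

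The active surveillance described favours finding events in DT and M+FE over control, with 36 scheduled classes against about 6 workshops. Contrasts of each exercise arm with control are therefore open to unequal ascertainment, most likely towards more recorded events with exercise. This part assumes that the article describes all the active surveillance there was. The self-report route weakens it by an unknown amount.

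Neither effect can be sized from the document. The figures of 54%, 21% and 4%, and of 3.0, 1.8 and 1.13, show what assumed rates would imply and are not estimates. The point should be addressed because Follow-up names safety as a purpose; it does not threaten the primary analysis.

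**What to change.** Record as an adverse event any untoward occurrence after randomisation, and grade it for severity. Keep the five present criteria as a separately named subset. Ask the same fixed question in all three arms at the existing week 12 and week 16 assessments, and report counts by assigned arm.

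Trial status gives recruitment as March to May 2023 and expected completion as March 2024, so those visits may have passed. In that case, tabulate by arm the symptoms reported through the route in Follow-up. State in the report that the recorded adverse events are a restricted subset, and that active surveillance was unequal between the exercise arms and control.

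The cost is a little more recording. A question at week 12 looks back over 12 weeks, so brief events will be recalled imperfectly. The cessation and ethics-reporting rules in Safety evaluation use the present definition. The sponsor must reconcile which events those rules refer to once the term is widened; no position is taken on the rules themselves.
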